**Statistical analysis**

***Sample size calculation***

Sample size calculation will be based on the mean HbA1c values (7.6±1.6 %) detected in the SFIDA population, consisting of 11,000 type 2 diabetic patients, aged 46-69 years, a HbA1c reduction of at least 0.5 % in EXE vs. CON group and a statistical power of 90% (α=0.05). To this end, 215 patients per arm need to be enrolled (430 patients total). Assuming a dropout rate of up to 25%, we will recruit 600 patients. Such a sample size also guarantees a statistical power of >90% to detect changes indicated for each of the parameters in the secondary endpoints.

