***Statistical analysis plan***

The c2 test for categorical variables and the Student’s t test or the corresponding nonparametric Mann-Whitney test for continuous variables will be utilized to compare patients’ characteristics at baseline. The efficacy of intervention on primary and secondary endpoints will be assessed using the unpaired t-test or the Mann Whitney U test for continuous variables, by comparing between-groups changes from baseline to end-of-study. For categorical variables (i.e. medications), logistic regression analysis will be applied, with end-of-study rate of use included in the model as the dependent variable and baseline rate of use and study arm included as covariates.

To account for change in medication throughout the 12-month period, multiple regression analysis will be performed, with baseline-to-end-of-study changes as dependent variable and treatment at baseline and treatment initiation during the study as dichotomous variables (yes versus no), whereas drug dosage will not be taken into consideration.

Within group end-of-study vs. baseline values will be compared using the McNemar test for categorical variables and the Wilcoxon signed ranks test for continuous variables. To identify independent predictors of HbA1c changes from baseline, a multiple regression analysis was applied, with mean value of METs, baseline HbA1c values, gender, age, and changes in HOMA-IR, BMI, waist, total, LDL-cholesterol and HDL-cholesterol, and hs-CRP as covariates forced in the model.

Multivariate analysis techniques (multiple or logistic regression) will be used to adjust for differences in the distribution of one or more parameters between the two arms, whereas the ANOVA trend test will be applied for evaluating the relationship of volume and intensity of exercise training (dose/response) and fitness variation with modifiable cardiovascular risk factors.

The likelihood to achieve glycaemic and nonglycaemic targets after 12 months will be estimated using logistic regression, adjusted for baseline status (on-target vs. not-on-target).

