| **F2** | Intermediate anthropometric and blood pressure measurements  Registration of results of intermediate, group B biochemical measurements (with eventual treatment regimen modification)  Registration of data from the diary of physical activity  Structured individualized counseling reinforcement  Prescription for intermediate, group B biochemical measurements |
| **F3** | Intermediate anthropometric and blood pressure measurements  Registration of results of intermediate, group B biochemical measurements (with eventual treatment regimen modification)  Registration of data from the diary of physical activity  Structured individualized counseling reinforcement |
| **F4** | Final anthropometric and blood pressure measurements  Collection of blood and urine samples for baseline, Group A biochemical measurements and forwarding to the central laboratory via express courier  Registration of data from the diary of physical activity  Administration of the SF-36 and the WHO-DTSQ questionnaires  Appointment at the Metabolic Fitness Center for metabolic fitness assessment and strength evaluation |

**Table 3:** Biochemical measurements

***Group A*** – to be performed at central laboratory (Laboratory of Clinical Chemistry, Sant’Andrea Hospital, Rome, Italy) at baseline and at the end of the study.

- HbA1c a, blood glucose b, C-peptide, and insulin levels c with calculation of the Homeostasis Model Assessment-Insulin Resistance (HOMA-IR) index from fasting glucose and insulin levels using the HOMA Calculator© software ([www.dtu.ox.ac.uk/homa/index.php](http://www.dtu.ox.ac.uk/homa/index.php));
- serum triglycerides and total and HDL-cholesterol levels b with LDL-cholesterol calculation using the formula: total cholesterol – [HDL-cholesterol + (triglycerides/5)];
- BUN, uric acid and serum creatinine b, with calculation of estimated glomerular filtration rate (eGFR) is calculated from serum creatinine by the modified Modification of Diet in Renal Disease Study Group equation ([www.kidney.org/professionals/KDOQI/gfr_calculator.cfm](http://www.kidney.org/professionals/KDOQI/gfr_calculator.cfm)), and urinary albumin d / creatinine b ratio in spot urine sample (these data are presented elsewhere);
- serum aspartate aminotransferase, alanine aminotransferase, -glutamyl-transpeptidase and creatine phosphokinase levels b;
- hs-C reactive protein b.

a High-performance liquid chromatography (Adams TMA1C HA-8160, Menarini Diagnostics, Florence, Italy).

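### The HbA1c predictor regression forces in total, LDL and HDL cholesterol changes without triglycerides, so by the protocol's own LDL formula the coefficient labelled total cholesterol is a triglyceride effect

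*Protocol*

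**What the plan says.** The Protocol, under Statistical analysis plan, describes a secondary model: "To identify independent predictors of HbA1c changes from baseline, a multiple regression analysis was applied". Its covariates are mean METs, baseline HbA1c, gender, age and "changes in HOMA-IR, BMI, waist, total, LDL-cholesterol and HDL-cholesterol, and hs-CRP as covariates forced in the model". Three lipid changes are therefore in the model together, none can be dropped by a selection step, and triglycerides are absent.

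Table 3 (Group A) states how LDL is obtained: "LDL-cholesterol calculation using the formula: total cholesterol – [HDL-cholesterol + (triglycerides/5". The value is calculated, not assayed. The same table says that the Group A tests are run at the central laboratory, "Rome, Italy) at baseline and at the end of the study", so the same formula supplies both values from which the LDL change is taken.

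Nothing else in the Protocol removes one of the three lipids from this model, adds triglycerides, or comments on the dependence among them.

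**The concern.** A regression meant to identify independent predictors is read coefficient by coefficient: each is taken as the association of the named variable with HbA1c change, the others held fixed. That reading fails when one covariate is a linear combination of two others and a fourth variable that is left out. Here the omitted variable is triglycerides, which is both an entry trait for the metabolic syndrome (Eligibility criteria) and a secondary outcome in its own right. A triglyceride association would be reported under another lipid's name, and the LDL and HDL coefficients would be shifted by the same amount in the opposite direction.

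**Working it through.** The Protocol gives no figure for this regression, so there is none to reproduce. The check is algebra on the stated formula, followed by an illustration of size.

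**1. The identity.** Let d denote change from baseline to end of study. The Table 3 formula is linear and is used at both times, so, apart from rounding of reported values,

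dTC = dLDL + dHDL + dTG/5.

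**2. What the coefficients mean.** Write the lipid part of the Protocol's model as b1·dTC + b2·dLDL + b3·dHDL and substitute:

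b1·(dTG/5) + (b1 + b2)·dLDL + (b1 + b3)·dHDL.

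Compare this with a model in dTG, dLDL and dHDL whose coefficients are g_TG, g_LDL and g_HDL:

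- b1 = 5·g_TG
- b2 = g_LDL − 5·g_TG
- b3 = g_HDL − 5·g_TG

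The two models span the same space, so fit and all non-lipid coefficients are identical. No assumption about the data is needed up to this point.

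**3. Numerical check.** Data were simulated for 450 patients, with true effects on HbA1c change of 0.003 per mg/dl for triglycerides, 0 for LDL and −0.005 for HDL, and a residual SD of 1. The SDs of change were 30 (LDL), 7 (HDL) and about 60 mg/dl (triglycerides).

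| Term | Protocol's list: coefficient (SE), t | Triglycerides in place of total: coefficient (SE), t |
|---|---|---|
| Total / triglycerides | 0.02078 (0.00406), 5.118 | 0.00416 (0.00081), 5.118 |
| LDL | −0.02183 (0.00446), −4.897 | −0.00104 (0.00180), −0.579 |
| HDL | −0.01793 (0.00737), −2.432 | 0.00286 (0.00680), 0.420 |
| R-squared | 0.0563 | 0.0563 |

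The ratio of the first-row coefficients is 5.000. LDL, which has no true effect, moves from t = −0.58 to t = −4.90. Its SE ratio is 0.00446/0.00180 = 2.5; for HDL it is 0.00737/0.00680 = 1.08.

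**4. Size of the LDL precision loss.** Since b2 = g_LDL − 5·g_TG, if lipid changes are uncorrelated with each other and with the other covariates,

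SE(b2)/SE(g_LDL) = √(1 + sL²/sT²),

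where sL is the SD of LDL change and sT is one fifth of the SD of triglyceride change. The SDs below (mg/dl) are assumptions.

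| SD LDL | SD triglycerides | sT | 1 + sL²/sT² | SE ratio |
|---|---|---|---|---|
| 20 | 100 | 20 | 2.00 | 1.4 |
| 20 | 60 | 12 | 3.78 | 1.9 |
| 20 | 40 | 8 | 7.25 | 2.7 |
| 30 | 100 | 20 | 3.25 | 1.8 |
| 30 | 60 | 12 | 7.25 | 2.7 |
| 30 | 40 | 8 | 15.06 | 3.9 |

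Allowing modest correlations (LDL–triglycerides 0.2, HDL–triglycerides −0.3, LDL–HDL 0.1) with HDL SD 7 raises the top of this range to √(19.52/1.07) = 4.3. By the same formula with HDL SD 7, the uncorrelated HDL ratio is at most √(1 + 49/64) = 1.33.

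**5. Adding rather than replacing.** With total, LDL, HDL and triglycerides all present, the simulated design matrix (intercept plus four lipids) has rank 4 for 5 columns, so the model cannot be fitted.

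**The case against.** Four counter-arguments deserve weight.

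- **The model can be fitted and its coefficients are valid partial effects.** This is correct. A reader might infer that LDL is computed from total and HDL alone and that the regression is singular. The Table 3 formula includes triglycerides/5, and that term is what keeps the model estimable. The defect is what the coefficients mean.
- **Total cholesterol loses no precision.** This stands too. A reader might compute a variance inflation factor for total cholesterol, for instance (900 + 25 + 144)/144 = 7.4 with assumed SDs of 30, 5 and 60 for LDL, HDL and triglycerides, and infer a loss that the fix would recover. It would not: b1 is five times the triglyceride coefficient with five times its SE, so t is identical. The loss relative to the corrected model falls essentially on LDL.
- **The wrong lipid is named only under a condition.** If triglyceride change has no partial association with HbA1c change, b1 is zero and the LDL and HDL coefficients are correct as labelled. That the model must mislead is therefore too strong a reading; that it does so whenever the triglyceride effect is not zero is correct.
- **The reach is small.** The Protocol's Endpoints section lists no goal on independent predictors of HbA1c change. The arm comparison uses a separate t-test or Mann-Whitney test, and the sample size does not depend on this model. The coefficients could also be re-expressed afterwards from the same fit.

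The last point limits the importance but does not remove the defect: the covariate list is explicit and forced, and nothing in the Protocol would prompt an analyst to re-express it.

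**Conclusion.** The point holds as an error of specification in one exploratory model. The relabelling in step 2 is exact and rests only on the stated LDL formula and on changes being taken between the two central-laboratory measurements. Its practical effect depends on triglyceride change being associated with HbA1c change, which the Protocol cannot tell us. The LDL standard error is inflated by roughly 1.4 to 4 times under the assumed SDs; the documents support the direction but not a particular value. HDL precision is little affected. A reader might infer a threat to the trial's main result, but the documents do not support that: the primary comparison, the sample size, the fit of this model and its non-lipid coefficients are all unchanged.

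**What to change.** In the covariate list, replace change in total cholesterol by change in triglycerides, so that the lipid terms are LDL, HDL and triglycerides. State that triglycerides replace total cholesterol and are not added to the three. The number of covariates and the fit stay the same, and each lipid coefficient then refers to the lipid it names. Dropping LDL and keeping total and HDL would also remove the dependence, but the total-cholesterol term would then mix LDL with triglycerides/5; in the simulation above that model's R-squared fell from 0.0563 to 0.0055. The cost is one term in the text: triglycerides are already measured centrally at baseline and end of study.

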***Secondary outcomes***

Secondary research goals include an exploration of :

- Percentage of patients in each group that after 12 month achieve one or more of the following targets: HbA1c <6.5% or HbA1c reduction >0.5%; total cholesterol <175 mg/dl; LDL cholesterol <100 mg/dl; HDL cholesterol >40 mg/dl; triglycerides <150 mg/dl; systolic blood pressure (BP) <130 mmHg; diastolic BP <80 mmHg; BMI reduction >1; waist circumference reduction >5 cm.
- Difference between groups in terms of reduction of HbA1c, serum triglyceride and LDL-cholesterol, systolic and diastolic BP, BMI and waist circumference and increment of serum HDL-cholesterol.
- Difference between groups in terms of reduction of number and/or dosage of glucose-, lipid- and BP-lowering drugs.
- Difference between groups in terms of reduction of global cardiovascular 10-year risk (UKPDS risk engine tables).
- Difference between groups in terms of improvement of well-being.
- Difference between groups in terms of direct medical costs and direct and indirect social costs.
- Dose/response relationship between the quality (volume and intensity) of exercise training and modifiable cardiovascular risk factors.
- Relationship between physical fitness at baseline and during the study and modifiable cardiovascular risk factors.

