# **Treatments**

***Exercise program***

The training program for the EXE group consists of twice a week supervised sessions of 75 min duration of mixed (aerobic and resistance) exercise, for 12 months.

Aerobic training will be performed using treadmill, step, elliptical, arm or cycle-ergometer. Transformation of maximal oxygen consumption (VO2max)in exercise load will be performed by the use of a software (Wellness System, Technogym SPA, Gambettola, Italy) or a dedicated spreadsheet, which allow calculation of the individual training load for each equipment from VO2max using the American College of Sports Medicine (ACSM) equations [21].

Resistance training will consist of 4 resistance exercises, i.e. thrust movement on the transverse plane (chest press or equivalent), traction movement on the frontal plane (lateral pull down or equivalent), squat movement (leg press or equivalent), trunk flexion for the abdominals, and three stretching positions. Intensity will be adjusted according to improvements in predicted VO2max and 1RM, as recorded throughout the study, thus resulting in further increments of working loads. In addition, caloric expenditure will be increased progressively by 0.1 kcal/kg body weight/session every month (Table 5).

Subjects in the EXE group will be allocated to either moderate-intensity aerobic (at 55% of predicted VO2max) and resistance (at 60% of predicted 1 Repetition Maximum, RM) or high-intensity aerobic (at 70 % of predicted VO2max) and resistance (at 80% of predicted 1RM) exercise, depending on the centres, which have been preliminary assigned to exercise patients at moderate- or high-intensity. Exercise and duration of aerobic training and number of series will be managed to obtain the same caloric expenditure per kg body weight, independent of the intensity level of exercise.

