**Measurements**

***Assessment of physical fitness***

Parameters of physical fitness, i.e. cardio-respiratory fitness, strength and flexibility, will be evaluated at baseline and at the end of the study by the estimation of VO2max, a 5-8 maximal repetition (MR) and a standard bending, respectively. In the EXE Group, measurements will be performed also during the study period, in order to adjust the training loads according to improvements in fitness parameters.

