***Assessment of physical activity***

Prospective assessment of the volume of non-supervised physical activity throughout the study will be accomplished by the use of a diary in which patients will report daily the type(s) of physical activity performed and the time spent in each of them (Figure 2). This diary is based on the range of physical activities considered in the Minnesota Leisure-LTPA questionnaire (Table 4). These activities will be divided in conditioning or volunteer (corresponding to LTPA) and non-conditioning or non-volunteer (including commuting, occupational and home activities) [24]. Volume will be calculated by multiplying the METscores corresponding to each Minnesota code [25], by time in hours per week spent in each activity, and expressed as METs . h-1 .week-1.

For supervised aerobic exercise, energy expenditure during supervised sessions will be calculated automatically by the machines from workload (i.e. the combination of speed and slope for treadmill, steps per minute for step and power for ergometer), using the ACSM’s equations [21] (Table 7). For supervised resistance exercise, since direct measurements in patients with low physical fitness such as T2DM subjects ([name] et al., unpublished results) did not confirm that energy expenditure varies with training intensity [25], we have decided on a conservative estimate of 3 METs/hour.

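### Exercise volume and fitness change are measured on continuous scales but are to be related to risk factors by an ANOVA trend test over groups, which gives up information in two exploratory secondary goals

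*Protocol*

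**What the plan says.** All references are to the protocol.

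- **The goals.** Secondary outcomes, introduced as an exploration, list "Dose/response relationship between the quality (volume and intensity) of exercise training and modifiable cardiovascular risk factors" and, separately, the relation of physical fitness to the same risk factors.
- **The test.** Statistical analysis plan: "the ANOVA trend test will be applied for evaluating the relationship of volume and intensity of exercise training (dose/response) and fitness variation" with those risk factors. The same sentence names multiple or logistic regression for a different purpose, adjustment for imbalance between the arms, and sets the trend test apart from it with the word whereas.
- **Volume.** Assessment of physical activity: "Volume will be calculated by multiplying the METscores corresponding to each Minnesota code" by the weekly hours spent. For supervised aerobic work, "energy expenditure during supervised sessions will be calculated automatically by the machines from workload".
- **Fitness.** Assessment of physical fitness: cardio-respiratory fitness, strength and flexibility are evaluated "by the estimation of VO2max, a 5-8 maximal repetition (MR) and a standard bending, respectively".
- **Intensity.** Exercise program: moderate or high, "depending on the centres, which have been preliminary assigned to exercise patients at moderate- or high-intensity".
- **Volume used uncut.** For predictors of HbA1c change, "a multiple regression analysis was applied, with mean value of METs, baseline HbA1c values, gender, age" and the changes in HOMA-IR, BMI, waist, cholesterol fractions and hs-CRP all forced in.

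**The concern.** To run the named test on volume or fitness change, the analyst must first cut a continuous exposure into ordered classes. Two patients at opposite ends of one class then count as equally exposed, while two on either side of a limit count as different. The protocol gives no reason for cutting, and its own HbA1c predictor model uses mean METs as they are.

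Two things are at stake. The first is power: when the relation is close to linear, a contrast over classes is less efficient than the regression slope. The second is the answer itself. A dose/response question asks how much a risk factor changes per MET-hour per week or per ml/kg/min of VO2max. A trend test returns mainly a p-value, and that p-value can move with the class limits.

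**Working it through.** **1. The plan's own figure.** The protocol states no power or effect size for the dose/response or fitness goals. The only calculation is for the primary comparison, based on "mean HbA1c values (7.6±1.6 %) detected in the SFIDA population", a 0.5% difference, 90% power and α = 0.05. With a two-sided test, n per arm = 2 × [(1.960 + 1.282) × 1.6 / 0.5]² ≈ 215.2, which agrees with the stated 215 (216 if rounded up). Recruiting 600 with 25% dropout leaves 600 × 0.75 = 450 completers, or 225 per arm. These two numbers are used as sample sizes below.

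**2. Efficiency of the grouped test.** Assume a normal exposure, a linear relation, k equal-sized classes and scores 1 to k. The relative efficiency e of the linear contrast against continuous regression is the squared correlation between the exposure and its class score. For tertiles of a standard normal exposure the class limits are ±0.431, where the density is 0.3636. The outer class means are ±3 × 0.3636 = ±1.091. With scores −1, 0, 1 the covariance is (2/3) × 1.091 = 0.727 and the score variance is 2/3, so e = 0.727² / (2/3) = 0.793.

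**3. Power.** Grouped power = Φ[(1.960 + z_ref) × √e − 1.960], where z_ref is 0.842 for 80% reference power and 1.282 for 90%. For tertiles at 80%: 2.802 × 0.891 − 1.960 = 0.535, and Φ(0.535) = 70.4%.

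| Classes | e | Power if regression has 80% (loss) | Power if regression has 90% (loss) |
|---|---|---|---|
| 2 | 0.637 | 60.9% (19.1) | 73.4% (16.6) |
| 3 | 0.793 | 70.4% (9.6) | 82.3% (7.7) |
| 4 | 0.856 | 73.6% (6.4) | 85.1% (4.9) |
| 5 | 0.888 | 75.2% (4.8) | 86.3% (3.7) |
| 10 | 0.935 | 77.3% (2.7) | 88.0% (2.0) |

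**4. Simulation check.** In 6,000 runs per setting, comparing the ANOVA linear contrast with regression at 90% reference power, the contrast had 81.7%, 85.5% and 86.2% for 3, 4 and 5 classes at n = 450, and 81.8%, 85.5% and 86.5% at n = 225. Both agree with the formula.

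**5. Sensitivity to the assumptions.**

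- *Reference power of 99%.* The loss for tertiles or quartiles is only 1 to 2 points.
- *Log-normal exposure (log SD 0.6 assumed), relation linear in raw volume, reference 80%.* The trend test has about 58%, 62% and 64% with 3, 4 and 5 classes. Regression on log volume would not keep 80% either. The squared correlation between raw and log volume is 0.36 / (e^0.36 − 1) = 0.36 / 0.433 = 0.83, so power is Φ(2.802 × √0.83 − 1.960) ≈ 72%.
- *Same exposure, relation linear in log volume.* Regression on raw volume has about 72%, against 70%, 74% and 75% for the trend test with 3, 4 and 5 classes. Here the grouped test matches or beats regression on the wrong scale.

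**The case against.** The strongest reply is that the protocol fixes no particular loss. The number of classes, their limits and the scores may stand in a statistical analysis plan that is not at hand, and their absence from the protocol is not a fault. This stands. A reader might take a loss of 5 to 10 points as a property of this plan, but the documents do not support that, since the loss depends on the number of classes, the reference power and the shape of the exposure. What the protocol does fix is the choice of test, and that choice is the point.

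A second reply is that grouping buys robustness. Unsupervised volume comes from self-completed diaries, supervised resistance work is credited at a flat 3 METs/hour, and a wrongly scaled regression can do no better than the trend test, as step 5 shows. This also stands in part. It argues for prespecifying the scale and checking outliers, not for relying on classes alone.

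A third is that pooled volume may be clustered by arm. EXE patients follow a common caloric target per kg and session (Table 5), while CON patients have no supervised sessions. The normal-exposure figures ignore this, and a pooled slope could largely repeat the randomised contrast. This is right, and any replacement analysis has to deal with it.

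Finally, the HbA1c model already uses mean METs uncut. It is only a partial answer. It covers HbA1c change alone, contains no fitness measure, and forces in changes in BMI, waist, HOMA-IR and other variables that may lie on the path from exercise to HbA1c, so its METs coefficient is not the overall dose/response slope.

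**Conclusion.** The point holds as a minor, inexpensive improvement. The plan assigns a test over ordered groups to exposures that it measures continuously, which loses information and gives no slope. With a roughly normal exposure, a linear relation and 80 to 90% power for continuous regression, the loss is about 4 to 10 points for three to five equal classes. With a skewed exposure, the size and even the direction of the difference depend on the scale on which the relation is linear.

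Three wider readings are tempting but unsupported:

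- *That intensity is affected too.* Prescribed intensity has only two levels, set by centre, so no continuous prescription is being cut.
- *That the trial's main result or size is weakened.* The primary HbA1c comparison does not use this test, and the 215 per arm reproduces.
- *That the loss contradicts the claim of more than 90% power for secondary endpoints.* That claim refers to the changes indicated for each parameter, and none is indicated for dose/response or fitness.

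**What to change.** In the Statistical analysis plan section, for exercise volume and fitness variation only:

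- Regress each risk-factor change on the continuous exposure, adjusted for the baseline risk-factor value and for study arm, or fit the model within arm. Report the slope with its confidence interval.
- Prespecify the scale of each exposure (raw or log MET-hours per week; change in VO2max, strength and flexibility).
- Add a quadratic or spline term as a check of linearity.
- Keep grouped means and the trend test for description.

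The cost is a change of analysis wording, with no new data and no effect on sample size. The small downside is that outlying self-reported diary values carry more weight in a regression, so a sensitivity analysis (transformed or rank-based) is needed.

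### The baseline on-target covariate is constant for the BMI and waist targets, so their planned adjustment drops out; for the absolute targets the yes/no coding is valid but gives up some power

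*Protocol*

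**What the plan says.** The last paragraph of the protocol's Statistical analysis plan covers "The likelihood to achieve glycaemic and nonglycaemic targets after 12 months" and names as its method "logistic regression, adjusted for baseline status (on-target vs. not-on-target". No target is exempted and no other covariate is named.

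The targets are listed under Secondary outcomes, first bullet. They are of three kinds:

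- **Absolute thresholds:** "total cholesterol <175 mg/dl; LDL cholesterol <100 mg/dl; HDL cholesterol >40 mg/dl", triglycerides below 150 mg/dl, and "systolic blood pressure (BP) <130 mmHg; diastolic BP <80 mmHg".
- **Changes only:** "BMI reduction >1; waist circumference reduction >5 cm".
- **Mixed:** "HbA1c <6.5% or HbA1c reduction >0.5" per cent.

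The protocol gives no absolute BMI or waist target. The BMI range and waist cut-offs under Eligibility criteria are entry conditions and are not called targets.

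**The concern.** A baseline on-target indicator makes sense only where a patient can be on or off target at entry. For a target defined as a reduction from baseline, the reduction at entry is zero for everyone. The analyst must then either improvise a model for BMI and waist or label as adjusted a result that is not.

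A second, milder issue arises where the indicator does exist. It puts a patient just above the threshold in the same class as one far above it, although their chances of reaching the target differ. The baseline value is collected anyway, so precision is given up for nothing. Target attainment is the first secondary outcome listed.

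**Working it through.** **The plan's own figure.** The protocol gives no figure for the target model, so I checked the sample size first. With SD 1.6 (from "mean HbA1c values (7.6±1.6" per cent), difference 0.5, two-sided alpha 0.05 and power 90%: n per arm = 2 × [1.6 × (1.960 + 1.282) / 0.5]² = 215.2. The plan states 215, and power at 215 is 90.0%. With 600 recruited and 25% dropout, 600 × 0.75 = 450 remain, or 225 per arm. The simulations below use 225 per arm.

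**BMI and waist (no assumption needed).** Change at baseline = 0, which is not a reduction of more than 1 unit or more than 5 cm. Status is therefore 0 for all patients. The design matrix with columns intercept, arm and status has rank 2 of 3: the status coefficient cannot be estimated, and the arm coefficient is that of the unadjusted model. Putting in the continuous baseline value gains little. Under one set of assumptions, power went from 68% to 69% (BMI) and from 76% to 77% (waist). In a second waist model (assumed SD 10 cm, effect 2 cm) it went from 56.7% to 60.8%, 72.9% to 74.3% and 93.5% to 94.3% at correlations of 0.7, 0.8 and 0.9.

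**Absolute threshold, HbA1c below 6.5% as the example.** Mean 7.6, SD 1.6 and effect 0.5 are from the protocol. The baseline-final correlation r is not given, so 0.3 to 0.8 is assumed. 3,000 trials per setting, Wald test of arm:

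| r | unadjusted | yes/no status | continuous baseline | gain, continuous over yes/no |
|---|---|---|---|---|
| 0.3 | 70.7% | 72.0% | 73.0% | 1.0 |
| 0.5 | 70.1% | 74.7% | 76.6% | 1.9 |
| 0.7 | 71.4% | 81.2% | 86.0% | 4.8 |
| 0.8 | 70.7% | 85.2% | 91.3% | 6.1 |

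With no effect, rejection was 4.2% to 5.5% for yes/no status and 4.6% to 5.3% for the continuous value.

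**Absolute threshold, systolic pressure below 130 mmHg.** All inputs except the threshold are assumed: mean 140, between-person SD 14, effect 4 mmHg, visit SD 6, 8 or 12. The implied correlation is 14² / (14² + visit SD²), from 196/232 = 0.84 down to 196/340 = 0.58. 1,500 trials per setting:

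| visit SD | yes/no status | continuous baseline | gain |
|---|---|---|---|
| 6 | 76% | 84% | 8 |
| 8 | 64% | 70% | 6 |
| 12 | 49% | 52% | 3 |

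Type I error was about 4% to 5% for both.

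**Mixed HbA1c target.** Given baseline b and no arm effect, the chance of success is Φ{[max(6.5, b − 0.5) − (7.6 + r(b − 7.6))] / [1.6 √(1 − r²)]}. At r = 0.5 and b = 7.0 this is Φ[(6.5 − 7.3) / 1.386] = 0.28; at b = 11 it is Φ[(10.5 − 9.3) / 1.386] = 0.81. Both patients are coded not on target. The spread is 0.27 to 0.89 at r = 0.3 and 0.26 to 0.57 at r = 0.8. At r = 0.5 the chance is 0.33 at b = 6.6, 0.28 at 7.0 and 0.41 at 8.0: it falls and then rises, so a straight line fits poorly. Power (1,500 trials per setting; 2,000 for r = 0.3):

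| r | yes/no status | linear baseline | knot at 7.0% |
|---|---|---|---|
| 0.3 | 70.2% | 73.0% | 74.4% |
| 0.5 | 80.4% | 79.9% | 82.9% |
| 0.6 | 88.6% | 88.1% | 90.2% |
| 0.7 | 93.7% | 92.5% | 94.4% |
| 0.8 | 98.6% | 98.1% | 98.7% |

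Simulation error on each power figure is about 1 point: at 80%, √(0.8 × 0.2 / 1,500) = 1.0%.

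**The case against.** The strongest reply is that little harm follows. For BMI and waist the constant term disappears and leaves a valid odds ratio. For the absolute targets the yes/no adjustment keeps its type I error and beats no adjustment, so preferring the continuous value is a matter of efficiency. The secondary goals are introduced as exploratory, the continuous changes are analysed separately, and the same section allows regression adjustment for differences between the arms. All of this stands. It limits the weight of the point but does not repair it: the general adjustment sentence does not name baseline BMI or waist, and the target model's covariate is fixed in the text.

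A reader might also infer more than the documents support:

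- **That the BMI and waist models fail or are biased.** They do not and are not; the redundant term is simply dropped.
- **That yes/no status is almost useless for the mixed HbA1c target.** This holds only near r = 0.5, where success is 0.48 for patients on target at baseline and 0.46 for the rest. At r = 0.7 it is 0.60 against 0.41, and at r = 0.8 it is 0.67 against 0.37.
- **That 8 or 9 points of power are lost for blood pressure and triglycerides in general.** Such figures come from single sets of assumed inputs.
- **That simulated powers below 90% refute the protocol's power claim for secondary endpoints.** The protocol gives no means, SDs or effects for these targets, and the figures here rest on assumed ones.

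**Conclusion.** The covariate is wrong as written for the BMI and waist targets. This follows from the definitions alone. The consequence is an unadjusted but valid odds ratio presented as adjusted, with about 1 point of power to gain from a baseline value in most settings tried and 4 at most.

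For the absolute targets, using the continuous value is a free improvement, not the correction of an error. It is worth about 1 to 6 points for an HbA1c threshold over r = 0.3 to 0.8 and about 3 to 8 points for systolic pressure. The direction was the same in every setting; the size depends on correlations and blood pressure inputs that the protocol does not give. For the mixed HbA1c target a linear term gains nothing at r = 0.5 to 0.8 and about 3 points at 0.3, while a flexible term gains about 0 to 5.

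The primary HbA1c comparison and its sample size are not affected.

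**What to change.** In the last paragraph of the Statistical analysis plan, replace the yes/no baseline status by: *adjusted for the baseline value of the same measure as a continuous covariate (for the HbA1c target, as a spline or with a knot)*. Add: *the BMI and waist targets are defined as changes and have no baseline on-target status*. The split by baseline status can stay as a descriptive table.

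The cost is two short text changes. The baseline values are already collected, and no patients or visits are added. The odds ratios become conditional on the baseline value, so they should be labelled as such and not compared directly with unadjusted ones.
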